#### Step 3: Strategies performed by the research team

Implementation of the HSS intervention will start with the school year 2021/2022 and include two cohorts of children and their parents. School nurses will undergo a 2-day MI training by trainers who are members of the Motivational Interviewing Network of Trainers (MINT) and receive four supervisions (Strategy 39: Conduct ongoing training) in the spring and early fall of 2021. Lectures on relevant themes in public health will be made available on the project website, and new school staff will be trained continuously as needed. A manual will be made available for the school health team (Strategy 5: Develop a detailed implementation plan) describing the background to the HSS, the theoretical basis, goals, measures, outcomes, the time plan and strategies. Educational materials will be provided (Strategy 41: Develop educational materials) including the health information brochure, teacher’s manual, children’s workbook and other written materials to be used by the school personnel and placed on the project website. Fidelity indicators to the intervention components and instructions how to monitor them will be communicated through the manual (Strategy 7: Develop instruments to monitor and evaluate core components of new practice). A checklist to assess the quality of delivery of implementation strategies will be developed (Strategy 6: Develop and organise a quality monitoring system) and used yearly by the research team during schools visits (Strategy 9: Monitor the progress of implementation effort). An open online homepage will be made available with all information needed by different stakeholder groups and continuously updated with relevant information. School staff will be directed to this site for assistance with technical or practical questions (Strategy 11: Centralize technical assistance).

After randomisation, schools allocated to group 2 will be introduced to the strategies in bundle 2 during a meeting with the research team. Each group 2 school will be offered a check-in to inquire about their progress and assist in problem solving. It will also be possible to ask questions via the website. Finally, efforts will be made to develop or identify an organisation that will be responsible for disseminating the program and support implementation (Strategy 75: Start a dissemination organisation). This will be based on stakeholder interviews and discussions with decision-makers.

#### Step 4: Defining outcomes and data collection methods

In step 4, the outcomes were defined, and instruments to measure them were selected. Reporting of the IMPROVE study results will follow the Standards for Reporting Implementation Studies StaRI guidelines [54] and the requirements of the Consolidated Standards of Reporting Trials (CONSORT) Statement [55].

### Primary outcome

Fidelity to the four components of the HSS will be assessed through 13 indicators (Table 4) based on the dimensions adherence, dose, participant responsiveness, and quality of delivery [56, 57]. This information will be gathered through attendance logs, questionnaires answered by school staff and parents, and audio recordings of MI sessions. The primary outcome will be operationalized as an adherence score and a responsiveness score to the four intervention components. Adherence to three of the four components will be reported by parents and the nurse as yes/no. The classroom component will be reported by the teachers, and thus the score for this component will be the same for all children in the same class. The total adherence score will be from 0 to 4. Participant responsiveness measures how parents respond to and are engaged in the intervention and is measured on a scale from 1 to 5 (no appreciation to full appreciation) for each component with a total score of 4 to 20. Dose refers to exposure or the amount of the classroom component that has been delivered and received. This information will be obtained from the teachers who will use a logbook to report the proportion of teaching sessions performed, the proportion of lesson completion including length, and whether any adaptations and are made. Quality refers to the MI component. All MI sessions will be recorded and a random 10% of each nurses’ interviews will be coded for MI competence using the MITI protocol 4.2 [58] by reliable coders. Those indicators not included in the two primary outcomes will be tested separately between the Basic and Enhanced group of schools.

**Table 4 Tab4:** Indicators of fidelity to the HSS components

Component	Adherence (%) (yes/no)	Dose (%)	Participant responsiveness (scale 1–5)	Quality of delivery
Brochure with health information	Parents reading the brochure (P)^a^	NA	Parents’ appreciation of the brochure (P)^b^	NA
Motivational Interview (MI)	Parents receiving MI (N)^a^	NA	Parents’ appreciation of health counselling (P)^b^	Quality of MI score coded according to MITI 4.2 (C)
Classroom component	Teachers providing the classroom component (T)^a^	Proportion of classroom lessons performed (T) Proportion of lesson completion (T)	Teachers’ perceived child involvement and engagement (T) Parent’s appreciation of the homework (P)^b^	NA
T2D test	Parents doing the test (P)^a^ Parents with a high risk that subsequently attend health care (P)	NA	Parents’ appreciation of the test (P)^b^	NA
**Total score**	Total sum score (0–4)	NA	Total sum score (4–20)	NA

Informants: *T* teacher; *C* coder; *P* parents, *N* school nurse

*NA* not assessed

^a^Included in the adherence score (primary outcome)

^b^Included in the responsiveness score (primary outcome)

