### Randomisation and blinding

Within each municipality, schools will be randomised 1:1 to group 1 (Basic: bundle 1) or group 2 (Enhanced: bundle 1 + 2) using a computer-generated assignment by an independent statistician after baseline measurement has been conducted in September 2021. It is not possible to blind school staff and the research team to allocation, but parents and children will not get this information. The CONSORT flow diagram with the number of schools and children is shown in Fig. 2.

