Promote network weaving (33)	13. Communication within and between primary health care centres 14. Time for administration in primary health care 15. Collaboration between primary care and school 16. New target groups 17. Early prevention 28. Sustainability of program	Send out yearly information letter to primary health care centres about the HSS program and the IMPROVE study. Encourage yearly meetings to establish social networks, promote information sharing, collaborative problem-solving and shared goals regarding family health	Research team	School health care and primary care
Provide ongoing consultation/coaching (44)	23. Providers’ attitudes towards the program 24. Providers’ competence and self-efficacy	Yearly audit and feedback through a written report on the fidelity score and performance of implementation strategies with coaching how to improve. E-mail sent four times per year to the school health team coordinator to offer assistance and help with problem solving	Research team	School personnel
Obtain and use student and family feedback (8)	23. Providers’ attitudes towards the program	Yearly feedback on parents’ attitude and perception of the program	Research team	School personnel

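### Half of the primary adherence score is reported by unblinded staff who deliver the component and, in the Enhanced arm only, are audited and coached on fidelity, with no stated check on their reports

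*Protocol article*

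**What the plan says.** Under Primary outcome, "The total adherence score will be from 0 to 4", with one yes/no point per component. The text says "Adherence to three of the four components will be reported by parents and the nurse as yes/no", and that teachers report the classroom component, so all children in a class share that value. Table 4 names the informant for each point:

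- brochure: "Parents reading the brochure (P)^a", parent;
- MI: "Parents receiving MI (N)^a", school nurse;
- classroom: "Teachers providing the classroom component (T)^a", teacher;
- type 2 diabetes test: parent.

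Under Randomisation and blinding: "It is not possible to blind school staff and the research team to allocation, but parents and children will not get this information".

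Table 3 (bundle 2), which Step 2 reserves for the Enhanced group, includes "Yearly audit and feedback through a written report on the fidelity score and performance of implementation strategies with coaching how to improve".

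The Primary outcome section also says "All MI sessions will be recorded"; the stated use is coding a random 10% of each nurse's interviews for competence. Limitations says that the indicators need further validation and gives classroom observation as an example. Neither source is tied to the adherence score, and Limitations does not discuss reporting that differs by arm.

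**The concern.** Two of the four points come from the people whose work the point describes. They know their arm. In one arm only, a fidelity score is fed back to them with advice on raising it. Table 3 does not define that score. Since the Primary outcome section operationalises fidelity as the adherence and responsiveness scores, the natural reading is that the feedback is, or contains, the primary outcome.

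Audit and feedback is a legitimate strategy, and staff cannot be blinded. The weakness is that the trial is scored on the audited staff's own reports when other sources are at hand. If coached staff become readier to answer 'yes', adherence rises in Enhanced without any change in delivery. Because the classroom point is shared, one teacher's answer moves a whole class. The choice of informant governs data collection, so a later analysis plan cannot recover a parent answer that was never requested.

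**Working it through.** **1. What differs by arm.** Basic schools also learn the fidelity indicators, through the manual (Step 3). The difference lies in the audit, the coaching and the other bundle 2 contacts: an introductory meeting, an offered check-in and four e-mails a year.

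**2. When it can act.** Table 5 (its layout is damaged in the text available) reads as fidelity collected in June 2022 for cohort 1 and June 2023 for cohort 2. A written report on cohort 1 scores can hardly precede the June 2022 measurement, so the audit route bears mainly on June 2023. Knowledge of allocation and the other contacts can act earlier.

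**3. The plan's own figures.** exp(0.3) = 1.35, exp(0.4) = 1.49 (stated as 1.5) and exp(0.5) = 1.65, so the planned odds ratios follow from the stated log odds. The stated powers (0.44, 0.66, 0.86) cannot be reproduced independently, because neither the assumed score distribution nor a design effect is given. They are not needed here.

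**4. Illustration with no true effect.** The documents give no item rates, so all rates below are assumptions: brochure 0.6, diabetes test 0.3, items independent. Let p be the true rate of a staff item and r the share of true non-deliveries reported as 'yes', in Enhanced only:

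reported rate = p + r(1 − p)

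mean shift in score = r[(1 − p for MI) + (1 − p for classroom)]

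At MI 0.7 and classroom 0.8 with r = 0.3, MI becomes 0.7 + 0.3 × 0.3 = 0.79 and classroom 0.8 + 0.3 × 0.2 = 0.86. The mean shift is 0.3 × (0.3 + 0.2) = 0.15. Expected proportions at scores 0 to 4:

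- Basic: 0.017, 0.139, 0.373, 0.371, 0.101
- Enhanced as reported: 0.008, 0.097, 0.353, 0.419, 0.122

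A proportional-odds fit to these two distributions gives an odds ratio of 1.35. Repeating the calculation:

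| True MI / classroom | r = 0.1 | r = 0.2 | r = 0.3 | r that gives OR 1.35 |
|---|---|---|---|---|
| 0.7 / 0.8 | 1.10 | 1.22 | 1.35 | 0.30 |
| 0.85 / 0.9 | 1.05 | 1.11 | 1.18 | 0.55 |

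Lower delivery throughout (brochure 0.5, MI 0.5, classroom 0.6, test 0.2) leaves more room: 1.19, 1.42 and 1.69, with OR 1.35 reached at r = 0.17. With the classroom item alone over-reported at 0.7 / 0.8, the same calculation gives 1.04, 1.08 and 1.12.

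**5. What a fixed percentage-point shift implies.** Adding 10 points to both staff items, with MI at 0.6 to 0.7, classroom at 0.8 and test at 0.3 to 0.4, gives an odds ratio of 1.47 to 1.50. The implied false-yes shares are 0.10/0.40 = 25% to 0.10/0.30 = 33% for MI, and 0.10/0.20 = 50% for classroom.

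**The case against.** A reader might infer that modest over-reporting would reproduce the protocol's middle scenario (OR 1.5), or that any Enhanced advantage in adherence would be an artefact. The documents support neither.

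- **Size.** Step 5 shows that OR 1.5 needs teachers to claim half of the undelivered classes and nurses a quarter to a third of the missed sessions, in one arm only. The Background section reports high fidelity for MI and for the classroom component in earlier trials, which suggests high true rates and little room for a false 'yes'. This is only a guide for MI, since external counsellors delivered it in the first two trials and nurses deliver it here. The objection stands against a single headline figure, which is why a range is shown.
- **The MI item is not a self-rating.** It records whether a parent received a session, a discrete event that should leave a recording. A false 'yes' is therefore detectable in principle. This stands and makes the classroom item the softer one. But the article does not say that recordings verify receipt.
- **Timing and scope.** The written report acts mainly at the second measurement, and responsiveness is scored by parents only. Both stand.
- **Existing checks.** Attendance logs, recordings and classroom observation are all mentioned, so it would be too strong to say that over-reporting could never be told apart from a real gain. But none is tied to the primary score or compared by arm.
- **Parents as a substitute source.** Seeing workbook tasks at home is not the same as a teacher delivering the lessons. This stands against replacing the teacher item, though not against using parent answers as a check.

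**Conclusion.** The concern holds as a risk of bias that could favour Enhanced in the adherence comparison. It is not a demonstrated bias. Three facts are firm: staff supply two of the four points, those staff are unblinded, and audit with coaching on fidelity goes to one arm. That the fidelity score fed back is the primary score, or contains it, is a reading of the text.

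At the two main sets of assumed rates, false-yes shares of 10% to 30% on both staff items give a spurious odds ratio of about 1.05 to 1.35, against planned values of 1.35 to 1.65. So the bias would usually fall short of a planned effect but could make up a material part of an observed one. The result rests on assumed delivery rates, independent items and no over-reporting in Basic. It describes the expected shift only and says nothing about precision under clustering. The point should be addressed because the sources for a check are largely in place.

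**What to change.** 1. Score the MI point as 'yes' when a dated recording of the session exists. Use the nurse's report only where there is no recording, and count those cases by arm.
2. Keep the teacher's report as the classroom item.
3. Add two yes/no questions to the existing end-of-year parent questionnaire: whether the parent had the MI session, and whether the child did the classroom or workbook activities.
4. Pre-state a sensitivity analysis of the adherence score based on the recording and parent sources, and report agreement between sources by arm at each measurement.

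Under step 1 a nurse's 'yes' without a recording still counts in the main score, so the protection comes from the flag and the sensitivity analysis. In that analysis such a 'yes' should count only if the parent confirms it.

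The cost is a tally of recordings already planned and a small questionnaire burden. Parent answers bring recall error and non-response, and parents may not distinguish MI from the routine nurse visit in which it is scheduled. That is why they serve as a check and do not replace the teacher item.

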### Secondary outcomes

#### Fidelity to implementation strategies

Fidelity to the implementation strategies deployed to support school personnel’s uptake and use of the intervention will be documented continuously by the research team. Once a year in May, the research team will visit each school to summarise the findings, alternatively through telephone calls. Assessing these outcomes will help to ensure that the implementation strategies are optimized and fit with end-users preferences. A checklist assessing the specific actions within each strategy will guide the assessment (Additional file 2). Each strategy will be graded as 0 = not implemented, 1 = partially implemented, 2 = fully implemented. Delivery of a strategy from the side of the research team will also be documented.

#### Acceptability, appropriateness, and feasibility

Monitoring of implementation outcomes will be done yearly with a validated and generic questionnaire developed by Weiner et al. that assesses acceptability, appropriateness, and feasibility of the HSS reported by school staff [59]. Each of these outcomes is assessed by four questions with a 5-point ordinal scale. The questionnaire will be answered individually by teachers, school nurses and principals involved in the intervention before the start and annually after that.

#### Organisational readiness to implement

This is a multi-dimensional construct that encompasses the willingness (motivation) and ability (capacity) of an entity to engage in an intervention and is considered to be a precursor of successful organisational change [22]. The results can guide internal discussions and helping identify ways to improve implementation of the HSS. School principals will answer the Leader Readiness to Implement Tool (LRIT) and school nurses and teachers will answer the Staff Readiness to Implement Tool (SRIT) adapted from the organizational readiness scale [60] by Cook et al. [61]. These tools were translated to Swedish and back-translated to English to assure correct translation. Both instruments contain 14 items on a 5-point Likert scale. Three scores will be calculated: A total readiness score, a change efficacy score, and a change commitment score.

#### Child height and weight

Child height and weight will be measured by the school nurse in pre-school class and again in year 2 including all children starting school in 2021 and 2022 (cohort 1 and 2) according to standard practice. We will use the extended international (IOTF) body mass index (kg/m^2^) cut-offs to define thinness, overweight and obesity [62]. The BMI z-score will be calculated according to a Swedish reference standard as described previously [29]. Weight and height data of all children that are routinely collected during health visits will also be obtained at the school level (de-identified, no consent needed) to be able to compare the weight status of study participants with all children at the same school.

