### Specific aims and hypothesis

The hypothesis is that the use of tailored implementation strategies with a focus on facilitation, monitoring, and feedback will lead to significantly better fidelity to the HSS intervention and to sustained effects on child and parent health outcomes. This study will be guided by the following research questions (question 1 has already been addressed):
What context-specific implementation determinants do stakeholders from municipalities in Sweden identify with regard to the implementation of the HSS program?Which of two bundles of tailored implementation strategies is most effective at improving fidelity, acceptability, appropriateness, feasibility, and organisational readiness to implement the HSS program?Does implementation of the HSS program at scale reduce social disparities in the proportion of children with overweight and obesity, and T2D risk among adults?What external implementation support will be needed to facilitate the sustainment of the program after the end of the study?

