In order to answer the question of whether implementation of the HSS program at scale reduces social disparities in child weight status parent’s T2D risk we will do as follows. The secondary outcomes analysed will be the change in prevalence of child overweight and obesity, children’s sex and age-adjusted BMI and parents’ risk of T2D. Dichotome outcomes will be analysed with a logistic regression model and continous outcomes with linear or quantile regression models. We will use a method able to account for the within-school and within-person clustering such as mixed models or generalised estimation equations (GEE). Parent country of birth and child sex will be explored as moderators of child and parent outcomes in addition to intervention fidelity and other school-related factors mentioned above.

Effects of implementation strategies on primary and secondary outcomes within-group will be assessed yearly relative to baseline using repeated measures analyses. All analyses will be conducted on an intention-to-treat basis. Sensitivity analysis will be carried out for primary and secondary outcomes after imputing relevant missing data, if relevant.

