### Ethical approval

This study was approved by the Swedish Ethical Review Authority (protocol number Dnr 2021–02267) on July 7, 2021. Written informed consent will be obtained from all participants in the study such as school and primary care staff and parents. Parents will be answering questionnaires, participating in recorded MI-sessions, and give permission to use routine data of their child’s height and weight.

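### The plan does not fix whether change in child overweight prevalence is analysed in all children or only in consenting families, and it gives the all-children data a comparison role only

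*Protocol article*

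**What the plan says.** Under Child height and weight, the school nurse measures children in pre-school class and "again in year 2 including all children starting school in 2021 and 2022 (cohort 1 and 2) according to standard practice". The same section then separates study participants from the whole school. Routine data on every child "will also be obtained at the school level (de-identified, no consent needed) to be able to compare the weight status of study participants with all" pupils of that school. No other use is given.

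Under Ethical approval, parents of participants "give permission to use routine data of their child’s height and weight". The eligibility section makes study participation voluntary, while every family is exposed to the programme as school routine.

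Under Specific aims and hypothesis, the third research question is: "Does implementation of the HSS program at scale reduce social disparities in the proportion of children with overweight and obesity" (it continues with diabetes risk among adults). Data management and statistical analysis takes up that question: "The secondary outcomes analysed will be the change in prevalence of child overweight and obesity", together with BMI and parents' diabetes risk. The models are to handle clustering within school and within person, and parent country of birth is a moderator. No analysis population is named there for the weight outcomes. The section closes with "All analyses will be conducted on an intention-to-treat basis".

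**The concern.** One outcome has two candidate populations, and the analysis text does not choose between them. The choice matters for two reasons.

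First, all children in the randomised schools receive the programme, so prevalence among consenters need not be prevalence in the schools. The article itself reports that parents in low-income areas were hard to engage, and workshop notes in its Table 1 expect low homework adherence and attrition in socioeconomically weak areas.

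Second, consent may depend on arm. Schools are randomised after the September 2021 baseline, and staff cannot be blinded. Cohort 2 families enter in autumn 2022. Getting families to consent is part of a bundle 1 strategy carried out by school personnel. Only Enhanced schools receive yearly feedback and coaching on how they perform the strategies. The tested intervention could therefore change who consents. Comparing participants with all children could reveal such selection but would not correct the between-arm estimate. An all-children contrast by randomised school does not depend on consent.

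**Working it through.** **1. Which population does the text imply?**

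| Place in the Protocol article | Content | Points to |
|---|---|---|
| Child height and weight, first sentence | Measurement of all school starters in both cohorts | All children |
| Child height and weight, last sentence | No-consent school-level data, for comparison | All children, descriptive use |
| Ethical approval | Permission to use the child's routine data | Consenters |
| Data management and statistical analysis | Within-person clustering; country-of-birth moderator | Linked records, so consenters |
| Specific aims, question 3 | Effect at scale | All children |

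Consenters are the likely analysis set. This is an inference, because no sentence says so.

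**2. The plan's own figure.** No sample size or power is given for child weight. The one checkable calculation on the consenting sample is power for the responsiveness score: 400 parents per group, SD 8, two-sided alpha 0.05 (assumed), power = Φ(δ / (SD·√(2/n)) − 1.96).
- δ = 0.8: Φ(1.414 − 1.96) = 0.293 (stated 0.29)
- δ = 1.6: Φ(2.828 − 1.96) = 0.807 (stated 0.81)
- δ = 3.2: Φ(5.657 − 1.96) > 0.999 (stated 0.99)

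The figures reproduce with n = 400 per group. The text does not say whether 400 is per cohort or over both.

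**3. Share of families covered**, taking one consenting parent per family. About 1400 families per school year over two cohorts gives 2800.
- 400 per group in total: 800/2800 = 28.6%
- 400 per group in each cohort: 1600/2800 = 57.1%

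**4. Illustration of selection on the level of prevalence.** The Discussion gives 22%, for ages 8–9. Let r be the consent rate of families of children with overweight relative to others (assumed; the documents give none). Prevalence among consenters = 0.22r / (0.22r + 0.78).
- r = 0.5: 0.110/0.890 = 12.4%
- r = 0.7: 0.154/0.934 = 16.5%
- r = 0.9: 0.198/0.978 = 20.2%

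This concerns the level. It does not show bias in change or in the difference between arms.

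**5. Precision of the between-arm difference in change.** SE = √(2 · 2p(1−p)(1−ρ) · DE / n), with DE = 1 + (n/15 − 1)·ICC. Inputs: p = 0.22; 15 schools per arm (30 schools, 1:1); within-child correlation ρ = 0.7 (assumed); ICC of change 0 to 0.05 (assumed). All children: 2800/2 = 1400 per arm. The constant is 2 × 2 × 0.22 × 0.78 × 0.3 = 0.2059. At ICC 0.02, DE is 1.513, 2.047 and 2.847 for n = 400, 800 and 1400.

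| ICC | SE, n = 400 | SE, n = 800 | SE, n = 1400 | Reduction from 400 | Reduction from 800 |
|---|---|---|---|---|---|
| 0 | 2.27 points | 1.60 | 1.21 | 47% | 24% |
| 0.02 | 2.79 | 2.30 | 2.05 | 27% | 11% |
| 0.05 | 3.43 | 3.05 | 2.87 | 16% | 6% |

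The 1400 column assumes that no child moves in or out; movement would shrink the gain.

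**The case against.** The strongest reply is that the analysis section leaves the population open, a detailed statistical analysis plan is promised, and naming the set for one secondary outcome commonly belongs there. The trial's primary outcome is fidelity, and child weight is only monitored. The planners also foresaw unrepresentative consent, which is why they collect the comparison data. Much of this stands and limits the weight of the point. What remains is that the article itself assigns the complete data a single, descriptive role, and a comparison cannot repair a contrast among consenters.

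A second reply is that question 3 asks about social disparities. Education and country of birth come from consenting parents, so school-level counts cannot answer that part. This is correct, and the linked data must be kept for it.

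Some stronger readings are tempting but not supported:
- A reader might infer that measuring all children conflicts with requiring permission. It does not: measurement is routine school health care, and permission concerns research use.
- A reader might infer that the intention-to-treat statement is breached. Analysing consenters by their school's allocated arm is an ordinary use of the term. Parents are not told the allocation, both arms receive the bundle that includes seeking consent, and no difference in consent between arms is shown.
- A reader might infer that the absent families are expected to benefit least. The article calls parents in low-income areas hard to engage and says nothing of that kind about benefit.

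**Conclusion.** The point holds in a limited form. The Protocol article does not fix the population for change in overweight and obesity prevalence. Its models and consent rules imply consenters, and the all-children data have no part in the between-arm analysis. For cohort 2, consent follows allocation and passes through unblinded staff, so a consenters-only contrast is open to selection and may not represent the schools.

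Its size is uncertain. It would be too strong to call the consenters a minority: the share is 29% or 57% depending on how 400 per group is read, and that figure counts parents in a fidelity power calculation, not children with weight data. No bias in change has been demonstrated. The precision gain at ICC 0.02 is about 27% against 400 per arm and about 11% against 800, and it rests on the assumed correlation and ICC. Representativeness is the main argument and precision the lesser one. The primary outcomes are not affected.

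**What to change.** In Child height and weight and in Data management and statistical analysis:
- Name the population for each weight result.
- Add a prespecified Basic-versus-Enhanced analysis of change in overweight and obesity prevalence from the all-children school-level data, by school and cohort, in pre-school class and year 2, adjusted for pre-school-class prevalence. It should stand at least as a sensitivity analysis beside the consenters' analysis.
- Keep the linked, consenting children for BMI z-score and for disparities by parental education and country of birth.

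The cost is some wording and one school-level model on data already to be collected. It needs no new consent, measurement or staff. The downsides are that the school-level data cannot be split by parental background and include some children who move in or out between the two measurements.
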